## Abstract

**Background:**

Parkinson’s disease (PD)-related constipation represents a prevalent and disabling non-motor symptom that imposes a substantial and growing health and economic burden worldwide. Current management strategies, including dietary modification, probiotics, and pharmacological therapies, often provide limited benefit, with potential adverse effects and minimal improvement in other PD-related symptoms. Acupuncture has emerged as a promising complementary therapeutic approach and has demonstrated preliminary clinical efficacy. However, the underlying biological mechanisms and the potential contribution of placebo responses to therapeutic effects remain insufficiently understood.

**Methods:**

This randomized controlled clinical trial will enroll 66 patients with PD–related constipation and randomly assign them in a 1:1 ratio to the real acupuncture group or the sham acupuncture group. Participants, acupuncturists, outcome assessors, and statisticians will be blinded to group allocation. The 8-week trial consists of a 4-week treatment period followed by a 4-week follow-up period. The primary outcome is the longitudinal change in the Chronic Constipation Severity Score (CCS) over time. Secondary clinical outcomes include weekly complete spontaneous bowel movements (CSBMs), spontaneous bowel movements (SBMs), Bristol Stool Scale (BSS) scores, and Unified Parkinson’s Disease Rating Scale (UPDRS) scores. In addition, exploratory outcomes include levels of short-chain fatty acids (SCFAs), histone deacetylase 1 (HDAC1), and phosphorylated *α*-synuclein at serine 129 (pS129-α-syn) measured in biofluid samples. Adverse events will be systematically monitored throughout the trial. The study is conducted in accordance with the SPIRIT guidelines.

**Discussion:**

This trial is designed to evaluate the clinical efficacy of acupuncture for PD-related constipation using a rigorously implemented double-blind, sham acupuncture-controlled design. Although the sham acupuncture procedure may itself induce nonspecific physiological and contextual effects, the use of a standardized double-blind control is intended to reduce expectancy-related bias and improve methodological rigor in the assessment of acupuncture-related outcomes. In addition to clinical symptom evaluation, the integration of SCFAs, HDAC1, and pS129-*α*-syn allows exploratory investigation of potential biological changes associated with treatment. This trial aims to provide multidimensional evidence regarding possible gut–brain axis–related mechanisms involved in acupuncture treatment for PD-related constipation.

**Trial registration:**

The study protocol was registered with the International Traditional Medicine Clinical Trial Registry (ITMCTR 2026000107) on December 7, 2025. The publicly accessible website is: https://itmctr.ccebtcm.org.cn/mgt/search.

## Introduction

1

Parkinson’s disease (PD) is a progressive neurodegenerative disorder that imposes an increasing burden on healthcare systems worldwide. According to the Global Burden of Disease trial, PD is estimated to affect approximately 11.67 million individuals globally and was responsible for around 420,000 deaths in 2023 (Guo et al., 2025). Constipation is a hallmark non-motor symptom of PD and may affect as many as 70% of patients with PD (Chiang and Lin, 2019). PD-related constipation should not be considered merely a gastrointestinal symptom but rather a clinical feature reflecting overall disease severity. Evidence suggests that patients with PD who experience constipation tend to present with more severe motor impairment and a greater burden of non-motor symptoms and generally exhibit poorer clinical outcomes (Yao et al., 2023; Adams-Carr et al., 2016). In addition, PD-related constipation has been associated with an increased risk of freezing of gait and falls (Mota Telles et al., 2025). Consequently, constipation in PD has emerged as a major public health concern worldwide. Current management strategies for PD-related constipation primarily include dietary modification, probiotics, physical activity, and pharmacological interventions (Ma et al., 2021; Andreozzi et al., 2024; Tan et al., 2021). Although these approaches have demonstrated varying degrees of efficacy in alleviating constipation symptoms, their benefits may diminish with disease progression or prolonged use, and some are associated with adverse effects (Zhang et al., 2023; Yin and Zhu, 2022). At present, there remains a need for additional safe and effective therapeutic options specifically targeting patients with PD-related constipation.

Acupuncture has been used in the management of constipation for several decades, prompting extensive investigation into its clinical efficacy and safety (Li et al., 2023; Wang et al., 2020). A high-quality study published in 2023 demonstrated that, compared with pharmacological therapy, acupuncture significantly improved constipation severity and stool characteristics, and alleviated motor symptoms in patients with PD (Li et al., 2023). Despite the growing body of evidence supporting the beneficial effects of acupuncture for constipation, only a limited number of studies have incorporated sham acupuncture as a control to examine potential placebo effects associated with acupuncture treatment. Blinding of acupuncturists is inherently challenging, and double-blind designs using validated sham acupuncture devices remain limited in studies of PD-related constipation. The underlying biological mechanisms remain incompletely understood. Emerging research has shown that patients with PD–related constipation exhibit alterations in gut microbiota composition accompanied by reduced levels of short-chain fatty acids (SCFAs) (Zhang et al., 2023). However, whether acupuncture exerts therapeutic effects on PD-related constipation through modulation of gut metabolic pathways has not been adequately explored in high-quality clinical studies. Therefore, this carefully designed randomized controlled trial incorporates a double-blind, sham acupuncture-controlled design to investigate the effects of acupuncture on patients with PD-related constipation. In addition, repeated assessments during the 4-week intervention and the subsequent 4-week follow-up will enable a systematic evaluation of the sustained effects of acupuncture on constipation severity and gut-related biomarkers.

## Methods

2

### Trial design and setting

2.1

This prospective randomized controlled trial was conducted in accordance with the principles of the Declaration of Helsinki and was developed in compliance with the Standard Protocol Items: Recommendations for Interventional Trials (SPIRIT) 2025 checklist (Chan et al., 2025). The trial is scheduled to be conducted from February 2026 to May 2027 at the outpatient acupuncture clinic of the First Affiliated Hospital of Guangzhou University of Chinese Medicine. The trial protocol has been approved by the hospital’s ethics committee (approval number: JY2025-164) and has been registered with the International Traditional Medicine Clinical Trial Registry (registration number: ITMCTR2026000107).

A total of 66 eligible participants will be recruited from the acupuncture outpatient department. After providing written informed consent, participants will be randomly assigned in a 1:1 ratio to one of two parallel groups: the real acupuncture group (*n* = 33) or the sham acupuncture group (*n* = 33). The intervention period will last for 8 weeks. Outcome assessments will be conducted at baseline, after the 4-week intervention, and after the 4-week follow-up. A flowchart illustrating the trial design is presented in Figure 1.

**Figure 1 fig1:**
[figure not shown]
Flow chart of the trial procedure.

### Participants

2.2

#### Inclusion criteria

2.2.1

Participants meeting all of the following criteria were eligible for inclusion:

Aged 45–80 years, with no restriction on sex.A clinical diagnosis of idiopathic PD according to the Chinese Diagnostic Criteria for Parkinson’s Disease (2016) (Liu, 2016), which requires the presence of bradykinesia combined with either rest tremor or rigidity, along with the absence of absolute exclusion criteria; And a diagnosis of functional constipation according to the Rome IV criteria (Mearin et al., 2016). Specifically, the Rome IV criteria require that patients present with at least two of the following symptoms: straining during more than 25% of defecations; lumpy or hard stools in more than 25% of defecations; sensation of incomplete evacuation; sensation of anorectal obstruction or blockage; manual maneuvers to facilitate defecation; and fewer than three spontaneous bowel movements (SBMs) per week.Hoehn and Yahr (H&Y) stage 1–3 assessed during the “ON” medication state, indicating that patients were in the early-to-middle stages of Parkinson’s disease without severe impairment of balance or walking ability.Continuous treatment with antiparkinsonian medications for at least 6 months, with a stable dosage maintained for a minimum of 2 months before enrollment.No use of medications that may affect gastrointestinal function, including probiotics, within 1 month before treatment. This 4-week washout period is consistent with the transient gut colonization of most probiotics (Zmora et al., 2018) and has been adopted in prior constipation trials (Janssen Duijghuijsen et al., 2024; Yoon et al., 2018).Ability to understand the trial procedures and provision of written informed consent voluntarily.

#### Exclusion criteria

2.2.2

Participants meeting any of the following criteria were excluded:

Presence of severe cognitive impairment or hallucinations that would interfere with reliable completion of clinical assessments.Participation in any other clinical trials involving pharmacological or acupuncture interventions within 1 month before enrollment.Presence of severe comorbid systemic diseases, including but not limited to organic gastrointestinal disorders (e.g., intestinal adhesions, intestinal obstruction, gastrointestinal tumors, or congenital malformations), immune system diseases, cardiovascular or cerebrovascular diseases, or hepatic or renal insufficiency.Previous receipt or planned treatment with deep-brain stimulation (DBS) during the trial period.Pregnant or planning pregnancy, or currently breastfeeding at the time of enrollment.A history of substance abuse (e.g., alcohol or drugs) within the preceding 6 months.A documented history of psychiatric disorders or the presence of psychotic symptoms.Fear of acupuncture that would preclude participation in the intervention.

### Sample size calculation

2.3

The primary outcome of this trial is the Chronic Constipation Severity Scale (CCS) score. Sample size estimation was based on data from a previous randomized controlled trial investigating acupuncture for patients with PD–related constipation (Lei et al., 2020; Zhen et al., 2021). In that trial, the mean CCS score after acupuncture treatment was 8.79 with a standard deviation (SD) of 4.63, whereas the control group showed a mean CCS score of 12.36 with an SD of 4.26. Sample size calculation was performed using PASS 2021 software, using a superiority test to compare two independent means. The significance level was set at *α* = 0.05 (two-sided), and the statistical power was 80% (1 − *β* = 0.80). Based on these assumptions and an anticipated 20% dropout rate, a total sample size of 66 participants was required to detect a statistically significant superiority in CCS scores between the two groups after the intervention. The sample size was powered for the primary clinical endpoint only.

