The acupuncture devices used in this trial were specifically designed and developed by the [name] PD Research Team (Figure 2). The disposable double-blind acupuncture device comprises a fixed blind-spot component and a needle body, and is available in four configurations based on skin penetration and insertion angle: real or sham needles with either vertical or oblique insertion. The real and sham needles are identical in external appearance, featuring an opaque design to prevent visual differentiation. The fixed blind-spot component is gourd-shaped and equipped with a custom adhesive base, allowing stable attachment to the skin surface. For real acupuncture, the needle tip is sharp, and a small slit at the bottom of the fixed blind-spot component allows the needle body (diameter × length: 0.35 × 50 mm or 0.35 × 65 mm) to penetrate the skin and elicit the intended acupuncture effect. In contrast, the sham needles have blunt tips and shorter needle bodies (0.35 × 42 mm or 0.35 × 36 mm), preventing skin penetration. However, the sham needles are sufficiently long to produce a mild pain, thereby maintaining participant blinding. In addition, a friction mechanism within the fixed blind-spot component provides resistance during insertion, preventing acupuncturists from distinguishing real from sham needles and thereby ensuring operator blinding. To evaluate the preliminary feasibility of operator blinding, a pilot validation test was conducted prior to the main trial. Ten acupuncturists with over 2 years of clinical experience performed the procedures and were asked to guess the needle type (real, sham, or uncertain). The distribution of responses did not suggest a clear ability to reliably distinguish between real and sham needles. Although limited by the small sample size, these findings provided preliminary support for the feasibility of operator blinding.

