Current therapeutic strategies for PD-related constipation primarily focus on promoting gastrointestinal motility to alleviate bowel symptoms. However, these approaches may be associated with adverse effects and generally provide limited improvement in other PD-related symptoms (Johanson and Kralstein, 2007). Acupuncture, a simple, safe, and widely accepted complementary therapy, has shown preliminary clinical efficacy in the treatment of PD-related constipation (Li et al., 2023). However, current research in this field is characterized by two major limitations. First, most randomized controlled trials have used levodopa therapy alone or levodopa combined with prokinetic agents as control interventions. Only a small proportion of studies have accounted for the potential placebo effects of acupuncture by employing sham acupuncture as a control condition. To our knowledge, no double-blind clinical randomized controlled trials investigating acupuncture for PD-related constipation have been identified in publicly available databases. This absence may partly reflect the procedural characteristics of acupuncture, for which acupuncturist blinding is inherently difficult to implement, thereby introducing a potential risk of bias. Second, most existing studies have relied primarily on subjective clinical rating scales as primary outcome measures, without incorporating objective biological markers or further exploring the underlying mechanisms of therapeutic effects. Exclusive reliance on subjective outcomes is susceptible to placebo effects, expectancy bias, and assessor bias and may obscure potential discrepancies between symptomatic improvement and the underlying pathological processes.

Against this background, the trial is designed as a high-quality randomized controlled trial to minimize the influence of placebo effects and expectancy bias, while simultaneously exploring potential mechanisms involving gut metabolic pathways. Based on prior evidence and clinical expertise, Sishen Needle and Intestinal Three-Needle (Tianshu [ST25], Guanyuan [CV4], and Shangjuxu [ST37]) were selected as the intervention acupoint sets. Both represent classic and widely applied components of Jin’s three-needle system and have demonstrated clinical relevance in the treatment of gastrointestinal dysfunction (Li et al., 2023; Li et al., 2023).

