To address methodological limitations in previous acupuncture studies, this trial innovatively employs a disposable double-blind acupuncture device developed by [name] research team. Identical intervention procedures are applied in both the real and sham acupuncture groups, with the only difference being the type of needle incorporated within the device. The real and sham devices are indistinguishable in appearance, and an embedded friction mechanism simulates tissue resistance during needle insertion, preventing acupuncturists from identifying needle type based on tactile feedback or visual cues. Furthermore, the sham needles are precisely engineered with controlled length and a smooth blunt tip, allowing participants to perceive mild pricking sensations without actual skin penetration. This design supports a double-blind approach in acupuncture trials and may help reduce subjective bias from both practitioners and outcome assessors while improving the rigor of placebo-controlled evaluation. However, it must be acknowledged that both real and sham acupuncture interventions may induce nonspecific physiological, placebo-related, and contextual effects, which should be considered when interpreting the results. As a consequence, between-group differences may be attenuated, and observed effects may not fully reflect the specific effects of acupuncture. Despite this limitation, the trial is expected to provide a more objective assessment of both the clinical efficacy and the associated biological changes of acupuncture in PD-related constipation. In addition, clinical biofluid samples are incorporated to capture objective biological responses to treatment. Given the central role of the gut in PD pathogenesis, fecal samples are collected to reflect gut microbial function associated with constipation. SCFAs, HDAC1, and pS129-*α*-syn are measured to evaluate changes in microbial metabolism, epigenetic regulation, and local pathological α-syn. Peripheral blood samples are simultaneously analyzed for HDAC1 and pS129-α-syn to explore potential systemic biomarker changes associated with acupuncture intervention.

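### The stated 80% power is conditional on a 3.57-point real-versus-sham difference, taken in full from an earlier trial whose control is not described, and section 2.3 does not say so

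*Protocol article*

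**What the plan says.** Protocol article, section 2.3: the planning values come from one earlier randomised acupuncture trial in the same condition. For the active arm it gives a mean of 8.79 and an SD of 4.63. For the comparator it says only this: "whereas the control group showed a mean CCS score of 12.36 with an SD of 4.26". The test is a two-sample superiority comparison of means, two-sided at 0.05 with 80% power. With 20% dropout this gives 66 participants, 33 per arm. The section does not describe what the source trial's control group received or how that trial was blinded.

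Section 2.4 makes this trial double-blind, acupuncturists included, and says of the comparator that "the sham needles are sufficiently long to produce a mild pain, thereby maintaining participant blinding". Section 2.5.2 keeps acupoints, frequency, duration and number of sessions the same in both arms.

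The Discussion (section 5) says, prefaced by an explicit reference to the authors' own knowledge, that "no double-blind clinical randomized controlled trials investigating acupuncture for PD-related constipation have been identified in publicly available databases". It also says that "most randomized controlled trials have used levodopa therapy alone or levodopa combined with prokinetic agents as control interventions", with sham used in only a small share of studies. It then notes that both kinds of needle may have nonspecific and placebo-related effects: "As a consequence, between-group differences may be attenuated, and observed effects may not fully reflect the specific effects of acupuncture".

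Section 4 provides least squares mean differences with 95% CIs as the output of post hoc comparisons that follow a statistically significant group-by-time interaction.

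**The concern.** The planning difference and the caution about attenuation sit in different sections and are never brought together. Section 2.3 gives 80% power without qualification, on a difference from a trial that was probably not double-blind. The Discussion says the contrast in the present design may be reduced. If the difference against this sham is smaller than 3.57 points, power is below 80%, and by how much depends on a quantity the article leaves open.

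What is at stake is how a non-significant CCS result would be read. Someone relying on an unqualified 80% could take it as good evidence that acupuncture adds nothing beyond sham, when the trial may have had limited power for a smaller specific effect. The interval that would show which effects remain compatible with the data is tied in section 4 to a significant interaction, so the text as written does not provide it in the case where it is most needed.

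**Working it through.** **Inputs (section 2.3).** Means 8.79 and 12.36; SDs 4.63 and 4.26; two-sided alpha 0.05; power 80%; dropout 20%; 1:1 allocation.

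**1. Reproduce the plan's figure.**
- Difference: 12.36 − 8.79 = 3.57.
- Pooled SD: √[(4.63² + 4.26²)/2] = 4.449.
- Standardised difference: 3.57/4.449 = 0.80.
- Two-sample t-test, noncentral t with df = 2n − 2 and noncentrality δ/(SD·√(2/n)). The smallest n per arm with at least 80% power is 26, where the noncentrality is 3.57/(4.449 × √(2/26)) = 2.89 and power is 81.0%.
- Dropout: 26/(1 − 0.20) = 32.5, rounded up to 33 per arm, 66 in total.

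This matches the article exactly. A normal approximation gives 25 per arm and 64 in total. So 66 corresponds to the full 3.57 points with no reduction.

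**2. Difference detectable with 80% power (same SD).**
- 26 evaluable per arm (full 20% dropout): 3.53 points, which is 3.53/3.57 = 99% of the planning difference.
- 33 per arm (no dropout): 3.12 points, which is 3.12/3.57 = 87%.

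**3. Power if the sham contrast is smaller.** The article does not quantify attenuation, so the first column is an assumption.

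| Attenuation (assumed) | Difference | Power, 26 per arm | Power, 33 per arm |
|---|---|---|---|
| 0% | 3.57 | 81% | 89% |
| 10% | 3.21 | 72% | 82% |
| 20% | 2.86 | 62% | 73% |
| 25% | 2.68 | 57% | 67% |
| 50% | 1.79 | 30% | 36% |

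If dropout does not exceed the planned 20%, power for a given difference lies between the last two columns.

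**4. Set the sections side by side.** The source is a randomised trial of acupuncture in PD-related constipation (section 2.3). The authors know of no double-blind randomised trial of that kind (section 5). Together these make it probable that the source was not double-blind. They do not settle what its control was.

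**The case against.** The strongest reply is that the source trial is not described, so a mismatch cannot be shown. The Discussion allows that some earlier trials used sham. In this article double-blind includes the acupuncturists, so a trial that was not double-blind could still have had a participant-blinded sham. In that case 3.57 would already be a sham contrast, and this design would mainly add operator blinding. This stands. A reader might infer that the source was certainly not double-blind, or that its control was drug therapy. The first goes beyond a general remark qualified by the authors' own knowledge; the second turns a statement about most trials into one about this trial.

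A reader might also infer that the protocol expects a smaller contrast than the one it is sized on. It does not say that. It says differences may be attenuated, as a caution about an active sham and without reference to the 3.57 points. Sections 2.3 and 5 therefore do not contradict each other.

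It is also fair that a detectable difference close to the assumed one is normal for any trial sized at 80%, that 33 evaluable per arm would absorb about 13% attenuation (1 − 3.12/3.57), and that the mixed model may gain some precision, although no correlation is given from which to credit it. The Discussion already asks for nonspecific effects to be considered in interpretation and lists the modest sample size as a limitation.

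What remains is narrower. The interpretive caution is never translated into power, section 2.3 does not say that its 80% depends on the borrowed difference holding against this sham, and section 4 attaches the interval to a significant interaction. A fuller analysis plan may report it regardless, but this article sets out the conditional rule.

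**Conclusion.** The sample size is correctly computed and 80% is right for its stated inputs. It is conditional on a difference of about 3.5 points against the double-blind sham with 26 evaluable per arm (about 3.1 with 33), and the article neither states that condition nor supports it for this comparator. How much power would be lost is unknown. Under assumed attenuation of 10% to 50%, power runs from 72% to 30% at 26 per arm and from 82% to 36% at 33 per arm. These are scenarios, not predictions; they use the source trial's SDs and a t-test at a single time point. The documents do not establish that the contrast will shrink, that the source lacked a sham, or that the trial is underpowered. They do support qualifying the power statement and securing an interval estimate for a non-significant result.

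**What to change.** Keep n = 66.

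- **Section 2.3.** State that 80% power is conditional on a 3.57-point CCS difference against the double-blind sham. Give the difference detectable with 80% power: 3.5 points with 26 evaluable per arm, 3.1 with 33. Show power over a range of attenuation, such as the table above, labelled as assumed.
- **Section 4.** Report the between-group CCS least squares mean difference with its 95% CI whether or not the group-by-time interaction is significant, and interpret a non-significant result from that interval.

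The cost is a few sentences and a small table, with no added patients or visits. The downside is a less favourable stated power.
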